## Abstract

**Introduction:**

Mental health disorders are common during pregnancy and the postnatal period and can have serious adverse effects on women and their children. The consequences for global mental health due to COVID-19 are likely to be significant and may have a long-term impact on the global burden of disease. Besides physical vulnerability, pregnant women are at increased risk of mental health problems such as anxiety, depression and post-traumatic stress disorder due to the consequences of social distancing. It can result in altered healthcare routines, less support from the family and friends, and in some cases, partners not being allowed to be present during prenatal visits, labour and delivery. Higher than expected, rates of perinatal anxiety and depression have been already reported during the pandemic. Pregnant women may also feel insecure and worried about the effects of COVID-19 on their unborn child if they get infected during pregnancy. Today, young urban women are used to using internet services frequently and efficiently. Therefore, providing mental health support to pregnant women via internet may be effective in ameliorating their anxiety/depression, reducing the risk of serious mental health disorders, and lead to improved maternal and perinatal outcomes.

**Overarching aim:**

Our aim is to explore the effectiveness of a web-based psychosocial peer-to-peer support intervention in reducing the risk and severity of perinatal mental health disorders and preventing adverse pregnancy outcomes among pregnant women living in metropolitan urban settings.

**Methods and analysis:**

We plan to conduct a multicentre prospective randomised controlled trial, Mental health of Urban Mothers trial. Pregnant women living in large metropolitan cities will be recruited using internet-based application through non-profit organisations’ websites. The women who consent will be randomised to receive a web-based peer-to-peer support intervention or usual care. Data will be analysed to identify the effects of intervention on Edinburgh Postnatal Depression Score and Generalised Anxiety Disorder 7 scores as well as pregnancy outcomes. The impact of COVID-19 pandemic on maternal stress will be assesed using Impact Event Scale-R. Any differences in outcomes between cities will be addressed in subgroup analyses.

**Ethics and dissemination:**

The study will be conducted according to the principles of Good Clinical Practice and will follow the ethical principles of the Declaration of Helsinki. The study protocol has been approved by the ethical review board of Chinese University of Hong Kong (IRB number 2019-8170) and Shanghai Center for Women’s and Children’s Health (international review board (IRB) number 2020-F001-12). The results will be disseminated at national and international scientific conferences, published in peer-reviewed medical journals and spread to the public through social media, news outlets and podcasts.

**Trial registration number:**

NCT04363177; Trial sponsor Karolinska Institute, CLINTEC, Stockholm, Sweden.

Strengths and limitations of this studyA evidence-based ‘Thinking Healthy’ intervention will be applied using state-of-the-art eHealth peer-to-peer support to elucidate the role of internet-based virtual consultation and psychosocial support on maternal mental health.Our multiprofessional research team will ensure ethical standards along with the quality of intervention, data collection and follow-up.An external data monitoring committee will monitor the trial and data quality.Due to the nature of intervention, investigators, as well as the study participants, will not be blinded to the intervention.Different cultures and healthcare systems in different study locations may have different impacts on pregnancy outcomes.

## Introduction

Pregnancy is a period of transition and great change, which may make some women more vulnerable to mental health problems. It is known that depressive symptoms during pregnancy may influence birth outcomes.^1–3^ The prevalence of postpartum depression (PPD) is increasing globally but varies considerably between different countries and cultures.^4 5^ In China, the prevalence of PPD in women of the one-child generation is reported to be higher compared with previous generations, particularly among women giving birth to a daughter.^6^ Prevalence rates are highest in the rural areas’ prefecture-level cities (25.4%), lower in the provincial capitals (19.5%) and lowest in the municipalities directly under central government (12.9%).^7 8^ Furthermore, there are substantial gaps in the accessibility of care.^2^ Perinatal mental health disorders may become more prevalent during a time of acute crisis, and the prevalence of maternal anxiety, distress and PPD can be expected to increase in China and elsewhere as a result of the COVID-19 pandemic.^9 10^ In this context, a recent study found that 35.4% of the participating women had an Edinburgh Postnatal Depression score (EPDS) >13.^11^ However, there might be cross-national differences in the risk factors and impact of pandemic on the prevalence of perinatal mental health disorders.

Some pregnant women might be predisposed to post-traumatic stress disorder (PTSD) during a crisis situation, such as the COVID-19 pandemic. Mothers who developed PTSD in response to the 9/11 terrorist attacks had lower morning and evening salivary cortisol levels, compared with mothers who did not develop PTSD.^12^ Beyond effects on the mother alone, perinatal mental health issues can have long-term effects on child’s mental and physical health as well as their behaviour and cognition.^13–17^ Distress in pregnant women may affect the foetus and is known to induce epigenetic changes in the placental genes.^18^ Increased risk of psychopathology is observed in children exposed to maternal prenatal distress. Elevated maternal cortisol and epigenetic regulation of placental glucocorticoid-pathway genes are potential mechanisms for these observations.^19^ Women often express feelings of inadequacy in the new mothering role, which can furthermore negatively impact their mental health and relationship to their infant.^20^

Effective treatments are needed to address high global rates of PPD with onset typically within 4 weeks after delivery^21^ and maternal depression up to 2 years after delivery.^22 23^ Programmes aimed at reducing PPD could achieve the most cost-efficient results by focusing efforts in the critical time periods around childbirth.^22^Web-based psychosocial support provided by trained public health nurses is an effective treatment method for PPD.^24^ Limited public health resources are challenges to the accessibility of mental health services, which is why the use of web-based psychosocial support could be a good alternative. Women perceive the risk for themselves or their infants to be above average during global crises, which increases the levels of uncertainty. However, face-to-face consultations during a pandemic are likely to increase the risk of disease transmission. Therefore, easily accessible eHealth support could provide fast and resource-effective care during the COVID-19 pandemic.

### Previous research

Screening programmes appear to be effective in identifying pregnant women at risk of developing perinatal mental health disorders,^25^ but they are neither universally implemented in public healthcare nor necessarily lead to effective interventions. One reason for the limited effectiveness is the small number of multidisciplinary perinatal mental healthcare teams that provide for the assessment and treatment of perinatal mental health disorders.^26^ Pregnant women in Shanghai reported a lack of access to resources and a strong preference for web-based psychosocial support. Previous studies suggested that women who received a peer support intervention were at half the risk of developing postnatal depression at 12 weeks postpartum than those in a control group.^27 28^ A recent systematic review has shown that therapist-supported internet-based cognitive behavaroral therapy (iCBT) significantly improves stress, anxiety and depressive symptoms among postpartum women, although the magnitude of effect was variable.^29^

There are challenges associated with supporting a family and raising children for young people living in modern metropolitan urban areas. These challenges may have a negative effect on maternal mental health. In Shanghai, China, a previous Randomized control trial (RCT) at the Obstetrics and Gynaecology Hospital of Fudan University concluded that a prenatal evidence-based psychosocial intervention model for high-risk pregnant women holds potential as a preventive programme that can address maternal health and improve birth outcomes.^30^ The mental health statuses of 6024 pregnant women were investigated when they registered for prenatal care from September 2015 to August 2016, where 23.89% and 9.44% had symptoms of depression and anxiety, respectively.^30 31^ There is a significant positive association between parity, depression, older age and risk of developing PPD.^32 33^ A cross-sectional study of 842 pregnant women with obstetric complications attending the same hospital reported that the prevalence of major and minor depression in high-risk pregnant women during antenatal period was 8.3% and 28.9%, respectively.^32^

Young couples in Hong Kong appear to have difficulties in balancing their traditional family roles and expectations with the hardships of living in a modern society. A recent study has found high levels of perinatal anxiety in families due to the financial burden caused by having children to honouring traditional family roles. Having children is highly encouraged and a sign of prosperity in a traditional Chinese family, yet, it is very expensive to raise even one child in Hong Kong.^34^ Having a high level of work–family conflict is a strong predictor of mental health problems across pregnancy. Family–work balance was also found to be notoriously poor in Hong Kong families, due to the extremely high demands of working hours. Dual-earner families in Hong Kong indicated that the work–family conflict was negatively related to job and life satisfaction. The study showed that the coping behaviours of Hong Kong employed parents were largely ineffective in solving problems related to work–family conflicts.^35^

## Objectives

### Purpose and aims

Our aim is to explore the effectiveness of a web-based psychosocial peer-to-peer support intervention in reducing the risk and severity of perinatal mental health disorders and preventing adverse pregnancy outcomes among pregnant women residing in metropolitan urban settings.

#### Primary objective

To investigate the impact of a web-based psychosocial intervention on EPDS among urban pregnant women living in Hong Kong and Shanghai.

#### Secondary objectives

To investigate the impact of a web-based psychosocial intervention on maternal anxiety levels assessed by Generalised Anxiety Disorder 7 (GAD7) scores.To explore the impact of COVID-19 pandemic on maternal stress levels assessed by Impact Event Scale (IES-R).To explore the impact of web-based psychosocial intervention on mental health and pregnancy outcomes among women from different socioeconomic and cultural environments.To explore the relationship between mental health status of pregnant women and rates of elective caesarean section on maternal request.

## Material and methods

### Trial design and setting

The Mental health of Urban Mothers trial is a prospective randomised controlled trial that will be performed in order to assess the effects of psychosocial support during pregnancy that focuses on factors that can reduce mental health problems and adverse outcomes in pregnant and postpartum women (intervention) versus standard care (control group). The intervention will be delivered by trained peers. Participating women will be recruited from two large urban areas, that is, Hong Kong (7.5 million inhabitants and among all maternity hospitals 11 027 annual deliveries^36^ and Shanghai (25 million inhabitants and Shanghai Maternity and Child Healthcare Hospital with more than117 700 deliveries per year). The intervention group will receive web-based psychosocial peer-to-peer support two times during the antenatal period before 36 gestational weeks (at 18–22 weeks and 24–28 weeks) and the control group will receive the usual standard antenatal care. Mental health status will be assessed using standard questionnaires, that is, EPDS and GAD7 and IES-R. Information on the course and outcome of pregnancy will be obtained by sending a questionnaire at 4–6 weeks postnatally via a web survey.

#### Hypothesis

Feelings of acute stress, anxiety, depression and more severe negative emotions such as PTSD that may lead to adverse pregnancy outcomes can be ameliorated by an appropriate internet-based psychosocial intervention started early in pregnancy, which will in turn influence the women’s overall mental well-being and improve pregnancy outcomes.

### Recruitment and blinding

Pregnant women will be recruited via non-profit organisation websites in each country. In addition to Hong Kong and Shanghai, we aim to include additional urban locations, including Stockholm, Sweden in this multicenter study. Via web link, the women will be guided to the research project website. The peer support website includes information about the project and informed consent. By completing the initial sociodemographic survey, the women can consent to participate in the research study. Then, they will ask to use an app to follow the study and complete the survey questionnaires. The participating women will be automatically randomised to intervention (peer-to-peer web-based psychosocial support) or control group (standard care) by the computer-generated random sequence. Regardless of recruitment to the intervention or control group, the women will continue their regular visits at the maternity clinics as usual.

Both the women and their peers will be forbidden to inform anyone in the study about which study group they belonged to. However, due to the nature of intervention, investigators, as well as the study participants, will not be blinded to the intervention.

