### Intervention

The intervention is a web-based psychosocial peer-to-peer support during pregnancy. It will be administered using WhatsApp and WeChat APP to contact pregnant women and provide psychosocial support over chat, call and video function.

The evidence-based eHealth peer-to-peer psychosocial intervention ‘Thinking Healthy’ will be tested in this RCT. In line with the WHO’s mental health gap (mhGAP) Intervention Guide, ‘Thinking Healthy’ is used to identify and manage perinatal mental health conditions (distress, symptoms of depression and anxiety) in non-specialised psychosocial support setting.^37^ ‘Thinking Healthy’ includes guidance on evidence-based interventions to identify and manage a number of priority mental health conditions. ‘Thinking Healthy’ has been widely used in low and low-middle income countries with limited mental health professionals.^38^ One of such priority conditions is perinatal depression. ‘Thinking Healthy’*”* also uses strategies (plans and activities) taken from iCBT^39^ to bring about a change in the mothers’ symptoms and functioning. The training does not turn the non-specialised health workers or trained peers into cognitive behavioural therapists—it only allows them to apply these strategies in their day-to-day work with women in the perinatal period. Non-specialised health workers or trained peers can practice ‘Thinking Healthy’.^40^ The research team provides support for the non-specialised healthcare workers and peers. In our RCT, the web-based psychological support will be provided by trained peers using diverse web-based tools, including video calls, chat messaging and voice calls for both women and their partners.

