### Data management

Each study participant will receive a study number for identification. Data will be collected continuously and through the smartphone application entered into an electronic case report system. Data will be encrypted and safely stored on an electronic server at the Karolinska Institute in Stockholm, Sweden in compliance with European general data protection regulation. Anonymised data will be extracted from the electronic case report system after data collection has ended and analysed for the different endpoints.

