### Statistical methods

Data will be analysed per protocol using an intention-to treat method. Average EPDS, GAD7 and IES-R scores will be compared between the intervention and control groups and across time points (prenatal and postnatal), using independent sample t-tests. Differences in proportions will be assessed using χ^2^ test. The non-normally distributed continuous variables will be analysed with the Mann-Whitney U test, and the results of the intervention will be analysed by Cohen’s effect size. Multiple imputations will be used for missing data. The variables used in the imputation mode will be previous EPDS score, education level and parity. All patients’ demographic data, retrieved from web survey, will be analysed by descriptive (mean, median and range) statistics. For categorical variables, absolute frequency, percentages and/or proportions will be calculated. χ^2^ or Fisher’s exact test will be used for comparison between groups. For the primary outcome measure, a two-sided p value of <0.05 will be considered significant. Subgroup analyses will be performed for several subgroups of EPDS scores. Spearman’s correlation test will be used to test the correlation between maternal antenatal mental health characteristics assessed by EPDS, GAD7 and IES-R at <34–36 weeks and at 6 weeks postpartum.

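### The reason given for leaving all investigators unblinded does not cover those who clean and analyse the data, who could work with a coded arm

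*Protocol article*

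**What the plan says.** Under Recruitment and blinding, the protocol article gives a general rule with its reason: "due to the nature of intervention, investigators, as well as the study participants, will not be blinded to the intervention". The strengths and limitations box, placed after the abstract, repeats it: "Due to the nature of intervention, investigators, as well as the study participants, will not be blinded to the intervention". Neither place makes an exception for any investigator role.

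Elsewhere the article describes how the trial runs:

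- Delivery (Trial design and setting): "The intervention will be delivered by trained peers".
- Link between team and delivery (Intervention): "The research team provides support for the non-specialised healthcare workers and peers".
- Allocation (Recruitment and blinding): women are "automatically randomised to intervention (peer-to-peer web-based psychosocial support) or control group (standard care) by the computer-generated random sequence".
- Outcome collection (Recruitment and blinding): women "use an app to follow the study and complete the survey questionnaires".
- Hand-over to analysis (Data management): "Anonymised data will be extracted from the electronic case report system after data collection has ended". Coding of the arm is not mentioned.
- Analysis (Statistical methods): score means are compared by t-test, and variables that are not normally distributed by Mann-Whitney test, with no criterion for deciding between them. In addition, "Subgroup analyses will be performed for several subgroups of EPDS scores", and these subgroups are not defined.

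**The concern.** The rule is wider than its reason. A psychosocial intervention given by a peer over chat or video cannot be hidden from the woman or the peer, and is hard to hide from staff who support the peers. But the rule covers every investigator. On a plain reading that includes whoever prepares and analyses the final data file, although nothing in the described conduct of the trial requires that person to know the arm.

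What is at stake is bias in the analysis. Because the women know their arm and rate their own EPDS, masking the analysis is one of the few protections against bias still open to this trial. Where the test and the subgroups can be settled after the data are seen, an analyst who knows the arms can also see, even without intending to use it, which option favours the intervention.

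**Working it through.** The question is mainly one of reasoning: for each role, does the nature of the intervention force knowledge of the arm?

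| Role | Source in the protocol article | Forced to know the arm? |
|---|---|---|
| Participant | Receives sessions or standard care (Intervention group; Control group) | Yes |
| Peer | Delivers the sessions (Trial design and setting) | Yes |
| Team members supporting peers | Work with those who deliver (Intervention) | Yes, in practice |
| Staff handling adverse events | Events linked to the intervention go to the principal investigator (Adverse events) | Yes, in practice |
| Person allocating | Automatic, computer-generated (Recruitment and blinding) | No such person is described |
| Outcome assessor | Women complete questionnaires in the app; pregnancy outcomes come by web survey (Recruitment and blinding; Trial design and setting) | The woman herself; no investigator rating is described |
| Those who clean and analyse the data | Anonymised extract after collection ends (Data management) | No |

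The last row is the one where rule and reason part.

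The same paragraph of Recruitment and blinding also forbids women and peers to reveal their group to others in the study. That ban makes sense only if some study personnel are meant not to know the arm, so it fits poorly with a rule that leaves all investigators unblinded.

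**Does masking change the design figures?** First, the plan's own sample size.

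- Inputs (Sample size and power calculation): mean EPDS 12.5, SD 4.0, difference 20%, power 80%, alpha 0.05. Two-sided testing is from Statistical methods.
- Difference: 0.20 × 12.5 = 2.5 points.
- Per arm: n = 2 × [SD × (z for alpha/2 + z for power) / difference]² = 2 × [4.0 × (1.960 + 0.842) / 2.5]² = 40.19. This is 41 if rounded up; the plan states 40.
- Power at 40 per arm: 79.8%.
- Per city: 2 × 40 = 80. The stated 100 implies 20% dropout, since 80 / (1 − 0.20) = 100. The rate itself is not stated.

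The plan's figure is reproduced to within one woman per arm. Masking enters none of these inputs, so 40 per arm and 100 per city stand.

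**The case against.** **The article does not say that analysts see the arm.** It names no analyst, and their status is inferred from the word investigators. A full protocol or analysis plan that is not shown might mask them. This stands as a limit. But the point does not rest on silence: the article states a rule without exception and gives a reason that does not carry it. If analysts are in fact masked, both statements misdescribe the trial and still need correcting.

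**Investigators have real routes to the allocation.** They support peers and receive adverse event reports, and the authors disclose the lack of blinding openly. This is right for those roles, which should stay unblinded. It does not extend to the analysis of the extract.

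**The open choices are better cured by prespecification.** The test choice is tied to distribution, and EPDS is described as normally distributed. This stands in part: prespecification is the direct remedy for undefined subgroups and a missing normality criterion. Masking supplements it, because it protects whatever is still unsettled when the data arrive.

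**Stronger readings that the article does not support.** A reader might infer that unblinded investigators could add cities because results look favourable. But data are extracted only after collection ends, no interim comparison is described, and further locations are already intended. A reader might also multiply 3 scales by 2 visits by 2 cities and take the 12 comparisons as the size of the problem. That is a count, not a measure of bias, and the article does not say that every scale is tested separately by city at each visit. Finally, a reader might call masking free, but someone outside the analysis has to hold the key.

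**Conclusion.** The concern holds for those who clean and analyse the data, and only for them. The stated reason justifies leaving unblinded the women, the peers and the team members who support peers or handle adverse events. It does not justify a rule covering all investigators.

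The bias at risk cannot be quantified from the article. It is confined to decisions made after the data are seen, chiefly the choice of test and the EPDS subgroups. Reporting bias in the self-rated EPDS remains whatever is done here.

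The conclusion assumes that the word investigators includes those who analyse the data, and that some team member can be kept outside the analysis to hold the key. The article gives no team structure to confirm either. The change is worth making because it is cheap and leaves sample size and power as they are, but it does not call the design itself into question.

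**What to change.** Reword the sentence in Recruitment and blinding, and the matching one in the strengths and limitations box, along these lines: participants, peers and the team members who support peers or handle adverse events are not blinded; those who clean and analyse the data are masked to the arm.

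In Data management, add that:

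- the arm is exported as a neutral A/B code;
- the key is held by an existing team member outside the analysis;
- the code is broken only after database lock and after the choice of tests, the subgroups and the data handling have been signed off.

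The cost is the rewording, a recoded variable at export, and a small organisational burden for the key-holder and the sign-off. Masking may be imperfect, since a large effect or process data left in the extract could reveal the arm.
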